### Statistics

#### Sample size calculation

The current trial was designed to verify the non-inferiority of HFRT combined with SIB compared to CFRT combined with sequential boost in patients undergoing BCS. The primary endpoint of the trial is LRR. Based on START A and B, the five-year LRR was 2.2%∼5.2% among patients treated with HFRT [8, 9]. In reference to WBI among Chinese population, a recent study comparing whole-breast HFRT and CFRT reported that the five-year LRR was 3.8% and 3.1% in CFRT and HFRT groups, respectively [24]. In our center, the five-year LRR in WBI patients without neoadjuvant systemic therapy was 2.8% [25]. Therefore, the five-year LRR of the CFRT group in the current trial is assumed to be 3% and the five-year LRR of the HFRT group is expected to be less than 5% (Hazard ratio [HR] of 1.68). With a study power of 80%, one-sided alpha value of 0.025, four-year recruitment period and five-year follow-up, at least 1383 participants will be required for each group, and 2766 participants required in total. Taking the withdrawal rate as 5%, the sample size will be 2904 (1452 for each group). The sample size was calculated using PASS2008.

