### Randomization

Participants with informed consent will be checked for eligibility before randomization. Eligible patients will be randomized into the HFRTsib group and the CFRTseq group in a ratio of 1:1. Stratified block randomization method will be applied and randomization will be performed with a randomization software designed by statisticians. The stratification factors of the randomization include age (≥ 50 vs. <50), ER status (positive vs. negative), axillary lymph node status (positive vs. negative) and adjuvant chemotherapy (yes vs. no).

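### The 5% withdrawal allowance was added as 2766 × 1.05 rather than 2766/0.95, so 2904 patients leave about 1379 per group, below the stated minimum of 1383

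*Protocol article*

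**What the plan says.** The Sample size calculation section of the protocol article first sets a minimum before any allowance for loss: "at least 1383 participants will be required for each group, and 2766 participants required in total". The next sentence converts this to the number to be randomised: "Taking the withdrawal rate as 5%, the sample size will be 2904 (1452 for each group"). It does not give the formula for the conversion.

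The minimum itself rests on these stated inputs: "With a study power of 80%, one-sided alpha value of 0.025, four-year recruitment period and five-year follow-up"; a five-year locoregional recurrence (LRR) of 3% in the control group; and a limit of 5% for the experimental group, given as a hazard ratio of 1.68. Allocation is 1:1 (Randomization section). The total of 2904 is repeated in the Abstract and in the Discussion.

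**The concern.** A withdrawal rate is a share of the patients who enter the trial. To keep a required number n after a proportion w has left, one randomises n/(1 − w). Multiplying by (1 + w) instead takes the 5% from the smaller, required number and always falls a little short. The figures 2904 and 1452 look like the product of that second calculation. If so, the planned size does not meet the minimum that the same section has just set.

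The stake is the internal consistency of the headline sample size. The calculation targets exactly 80% power and states no reserve beyond this allowance, so a reader who applies the 5% will find the retained number below the requirement. The question is whether the shortfall matters for power.

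**Working it through.** **Inputs**, all from the Sample size calculation section unless noted: required n = 1383 per group, 2766 in total; withdrawal w = 5%; final size 1452 per group, 2904 in total; one-sided alpha 0.025; power 80%; four-year accrual and five-year follow-up; five-year LRR 3% in the control group, limit 5%; 1:1 allocation (Randomization section).

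**1. Is the base figure of 2766 sound?**
- Hazard ratio at the limit: ln 0.95 / ln 0.97 = 1.684, which agrees with the stated 1.68.
- Events needed (Schoenfeld): 4 × (1.960 + 0.842)² / (ln 1.684)² = 115.6, so 116.
- Event probability, assuming an exponential hazard λ = −ln 0.97 / 5 = 0.00609 per year in both groups, uniform accrual over R = 4 years and at least F = 5 years of follow-up: 1 − [exp(−λF) − exp(−λ(R + F))] / (λR) = 0.0417.
- N = 116 / 0.0417 ≈ 2780 (about 2770 with the unrounded 115.6 events).

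This is within 0.5% of 2766. The base figure reproduces and is not in question.

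**2. How was 2904 obtained?**

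| Rule | Total | Per group |
|---|---|---|
| n × 1.05 | 2766 × 1.05 = 2904.3 | 1383 × 1.05 = 1452.15 |
| n / 0.95 | 2766 / 0.95 = 2911.6, so 2912 | 1383 / 0.95 = 1455.8, so 1456 |
| Stated | 2904 | 1452 |

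The stated figures match the first rule, rounded down. They do not match the second.

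**3. What remains after 5% withdrawal?**
- Total: 2904 × 0.95 = 2758.8, against 2766 required, so about 7 short.
- Per group: 1452 × 0.95 = 1379.4, against 1383 required, so about 4 short.
- Withdrawal that 2904 does cover: (2904 − 2766) / 2904 = 138 / 2904 = 4.75%.
- Extra randomised patients under n/0.95: 2912 − 2904 = 8 (0.3%).

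**4. What does it do to power?** Take the worst case, in which withdrawn patients contribute no follow-up. With the event probability of 0.0417, Schoenfeld power is Φ(½ √d × ln 1.684 − 1.960), where d is the number of events.
- 2766 retained: d = 115.4, power 79.9%.
- 2758.8 retained: d = 115.1, power 79.8%.

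The loss is about 0.1 percentage point.

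**The case against.** The best counter-argument is that withdrawn patients are not lost entirely. LRR is to be estimated by cumulative incidence, and the Statistical analysis section also names the log-rank test and Cox regression; in such methods a patient counts until censored. As an illustration, suppose the 5% withdraw uniformly over their follow-up, with the other assumptions as above. Then 2904 randomised patients yield about 118.2 events, equivalent to about 2832 fully followed patients, and power is about 80.9%. On that reading the trial is not short of information. This stands, and it is why the finding must not be read as a claim that the trial is underpowered. It does not repair the text, because the section states a minimum number of participants and then an allowance in participants, and on those terms 5% of 2904 is too many to lose.

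Two further points are fair but separate:
- Rounding the hazard ratio moves N by more than this slip does: about 2796 with 1.68 against about 2770 with 1.684.
- The Discussion gives recruitment from June 2018 to June 2024, six years rather than the four used in the calculation. With six-year accrual the event probability rises to 4.75%, and 2758.8 fully followed patients would give about 84.7% power. The benchmark of 1383 would itself change once that input is updated.

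Both confirm that the practical effect is negligible. Neither makes the stated allowance correct. Nor is this a detail that a journal article may leave to the full protocol: it is a printed figure that does not meet the requirement printed just before it.

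**Conclusion.** The concern holds as a minor arithmetic error. The figures 2904 and 1452 come from multiplying by 1.05, and 5% withdrawal from them leaves about 1379 per group, under the stated 1383. The size is 8 randomised patients, or about 7 retained. The power cost is about 0.1 point if withdrawn patients contribute nothing, and less if they are followed for part of the time.

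The head-count result rests only on reading the withdrawal rate as a share of those randomised, which is its ordinary meaning; the section names no other denominator. The power figures rest in addition on an exponential hazard, equal true rates in the two groups, and the four-year accrual in the calculation. The conclusion that the effect is negligible does not depend on these details.

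**What to change.** Keep 2904 and correct the sentence. Either of these would do:
- state that 2904 patients (1452 per group) allow for 4.75% withdrawal; or
- state that with 5% withdrawal about 1379 per group would remain, with power of 79.8% on the plan's assumptions.

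No change to recruitment, design or analysis is needed. The cost is one figure in the text. The natural moment is when the sample size section is next revised to reconcile its four-year accrual with the six years in the Discussion; any allowance recalculated then should divide by 0.95.

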#### Statistical analysis

The primary endpoint LRR will be estimated with the cumulative incidence method. Distant metastasis-free survival, DFS and OS will be calculated using Kaplan-Meier method. Differences of the survival outcomes between HFRTsib and CFRTseq groups will be compared with the log-rank test and analyzed by the COX regression model. Acute and late toxicities will be described as frequency and severity. Comparison of toxicities and cosmetic results between the two groups will be performed with the Chi-square test.

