#### Secondary endpoints

Disease-free survival (DFS), overall survival (OS), incidences of acute and late adverse events, cosmetic outcomes and quality of life (QoL) will be compared between the two groups of HFRTsib and CFRTseq.

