### Eligibility criteria

#### Inclusion criteria

Female patients aged between 18 and 70 years.Single tumor or multiple tumor that could be removed by one quadrantectomy.Receiving BCS with negative surgical margins.Receiving sentinel lymph node biopsy and/or axillary lymph node dissection. If sentinel lymph node is positive, axillary lymph nodes should be dissected at stations I and II. The total number of nodes dissected should be at least ten.Tumor bed can be outlined by metal markers placed during surgery or postoperative changes can be clearly identified on CT.Histology confirmed invasive breast cancer with pathological classified T1 ∼ 3N0 ∼ 3M0.The status of estrogen receptor, progesterone receptor, human epidermal growth factor receptor 2 and Ki-67 were determined by immunohistochemistry.No distant metastasis before radiotherapy.No history of serious medical disease or other serious comorbidities, such as psychiatric and allergy history.Karnofsky performance score (KPS) of 80 or higher.Provision of written informed consent.

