### Follow-up

Regular follow-up visits will be scheduled every three months during the first year after RT, every six months for two to five years after RT, and annually thereafter. Acute radiation toxicity will be evaluated before, during, at the end of, and three months after RT. Late radiation toxicity will be assessed before RT, three months after RT, and then annually. Acute toxicity will be graded according to the Cancer Institute’s Common Terminology Criteria for Adverse Events version 4.03 (CTCAE 4.03) and the Radiation Therapy Oncology Group (RTOG) radiation morbidity scale. Late toxicity will be evaluated primarily based on the RTOG late radiation morbidity scale and the LENT-SOMA scale [21, 22]. Cosmetic outcomes will be scored by patients, research nurses and physicians respectively using the Harvard Scale system [23]. QoL assessment will be performed using EORTC-QLQ-C30 and QLQ-BR23 questionnaires. All the case report forms will be documented by the researchers and those who were authorized by the researchers. The case report forms and other related data will be preserved for at least five years after the completion of the trial.

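### Toxicity is graded before radiotherapy, but the stated unadjusted Chi-square comparison gives that pre-treatment grade no role

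*Protocol article*

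**What the plan says.** Toxicity is a secondary endpoint. Under Secondary endpoints, the "incidences of acute and late adverse events, cosmetic outcomes and quality of life (QoL) will be compared between the two groups".

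The Follow-up section puts a baseline into both schedules: "Acute radiation toxicity will be evaluated before, during, at the end of, and three months after RT", and "Late radiation toxicity will be assessed before RT, three months after RT, and then annually". On grading it says: "Late toxicity will be evaluated primarily based on the RTOG late radiation morbidity scale and the LENT-SOMA scale".

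The Statistical analysis section then has two sentences on toxicity. The first is descriptive: "Acute and late toxicities will be described as frequency and severity". The second gives the test: "Comparison of toxicities and cosmetic results between the two groups will be performed with the Chi-square test". Neither mentions the pre-RT grade. Neither says whether the compared quantity is the worst grade, prevalence at a visit, or a grade new or worse than baseline.

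The article states no effect size, margin or power for toxicity.

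**The concern.** Every patient has had breast-conserving surgery and a sentinel node biopsy, an axillary dissection or both. The Inclusion criteria add: "If sentinel lymph node is positive, axillary lymph nodes should be dissected at stations I and II", with at least ten nodes removed. Adjuvant chemotherapy is a stratification factor, although the article gives neither its frequency nor its timing relative to RT. Some breast, arm and shoulder effects can therefore be present before the first fraction, and a grade alone does not separate a surgical cause from a radiation cause.

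The node-positive patients, who may have had the fuller axillary surgery, are also those who receive regional node irradiation (Target volumes definition). The Background section names arm and shoulder symptoms as an outcome of interest for that treatment.

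If the Chi-square test is run on all graded effects, patients whose grade never changed after RT enter the table as events in both arms. They carry no information on fractionation, but they add variance and move the ratio of the two rates towards one. The article intends to report on the tolerance of the shorter course (end of the Discussion), so a lower chance of seeing a real difference matters.

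**Working it through.** The article has no figure for the toxicity comparison to reproduce. The calculation below illustrates how much the choice could matter.

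**Inputs**
- Group size (Sample size calculation): 1452 per group less 5% withdrawal, 1452 × 0.95 = 1379. Allocation is 1:1 (Randomization).
- RT-induced rates of one late effect at or above a threshold: 8% and 11%. Assumed.
- Pre-RT prevalence b of the same effect: 0, 5, 10 and 20%, equal in both arms. Assumed.
- Pre-RT effects persist to the late assessment and are independent of RT-induced ones. Assumed.
- Two-sided 5% test of two proportions, no continuity correction.

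**Formulas**, with p the induced rate:
- Baseline effects counted: rate = b + (1 − b)p.
- Only new events counted, all patients in the denominator: rate = (1 − b)p.
- Under both rules the absolute difference is (1 − b)(p2 − p1).
- Power = Φ[(difference − 1.96 × SE0)/SE1], where SE0 uses the pooled rate and SE1 the two separate rates.

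**Worked case, b = 10%**
- Counted: 0.10 + 0.90 × 0.08 = 17.2% and 0.10 + 0.90 × 0.11 = 19.9%. Difference 2.70 points, ratio 19.9/17.2 = 1.16. SE0 = 0.01480 and SE1 = 0.01479, so power = Φ[(0.0270 − 1.96 × 0.01480)/0.01479] = 45%.
- New only: 0.90 × 0.08 = 7.2% and 0.90 × 0.11 = 9.9%. Difference 2.70 points, ratio 9.9/7.2 = 1.375. SE0 = 0.01065 and SE1 = 0.01064, so power = Φ[(0.0270 − 1.96 × 0.01065)/0.01064] = 72%.

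| Pre-RT prevalence | Difference, either rule | Rates, baseline counted | Power, counted | Rates, new only | Power, new only |
|---|---|---|---|---|---|
| 0% | 3.00 points | 8.0% vs 11.0% | 77% | 8.0% vs 11.0% | 77% |
| 5% | 2.85 points | 12.6% vs 15.5% | 58% | 7.6% vs 10.5% | 74% |
| 10% | 2.70 points | 17.2% vs 19.9% | 45% | 7.2% vs 9.9% | 72% |
| 20% | 2.40 points | 26.4% vs 28.8% | 29% | 6.4% vs 8.8% | 66% |

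Counting baseline effects therefore costs about 17, 27 and 37 percentage points of power. The loss comes from variance: the absolute difference is the same under both rules.

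**Sensitivity to the assumed rates.** The only late-toxicity rates in the article are 11.5% and 10.6%, for moderate or marked breast induration in a cited trial (Discussion). With 11.5% against an assumed 15%, 1379 per group and b = 10%, power is 52% with baseline effects counted and 72% with new events only. With 5% against 8% at the same b, it is 49% and 86%. The direction is stable; the size depends on the assumptions.

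**The case against.** The strongest reply is that nothing here is stated wrongly. The text never says that all graded effects enter the table. The endpoint is worded as incidences, which can mean new occurrences. A pre-RT assessment is most naturally collected to serve as a reference, and a Chi-square test works equally well on new or worsened grades. The article is condensed, no statistical analysis plan is shown, and baseline handling for a secondary safety endpoint is often settled there.

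Most of this stands, and it limits the point in three ways.

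- A reader might infer that the plan does count existing surgical effects as radiation toxicity. The documents do not support that; it is one of two readings of the same sentences.
- A reader might infer that the result would be biased in favour of one arm. Allocation is randomised 1:1 and stratified by nodal status and adjuvant chemotherapy, so pre-RT effects are balanced on average. The consequence is attenuation and lost power on a secondary endpoint for which no power is claimed. The non-inferiority margin concerns locoregional recurrence only, and the article does not say that a non-significant toxicity test will be taken as proof of equal safety.
- A reader might expect the change to restore the power and difference seen with no baseline effects (77%, 3.0 points). It does not: power becomes 74%, 72% or 66%, and the difference stays at 2.85, 2.70 or 2.40 points.

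What the reply does not remove is that the article names a specific test, and that test as named has no place for a measurement it schedules for every patient. A better comparison is available from data already being collected.

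**Conclusion.** The point holds as an improvement to a stated analysis, not as a demonstrated error. Acute and late toxicity are graded before RT, and the stated between-arm comparison is an unadjusted Chi-square test that gives this grade no role. If the test is applied to all graded effects, power to detect a toxicity difference falls. In the illustration it is 58%, 45% or 29%, against 74%, 72% or 66% with new events only, at a pre-RT prevalence of 5%, 10% or 20%.

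These figures rest on assumed induced rates, an assumed prevalence, and pre-RT effects that persist and are independent of RT-induced ones. The documents supply none of these, so the true size is unknown. If the sponsor already intends to count only new or worsened grades, the loss does not arise and only the wording needs to say so. The primary endpoint is unaffected.

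**What to change.** State in the analysis text how the pre-RT grade enters the comparison. Either of two forms would do, for acute and late toxicity alike:

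- For each toxicity item, define an event as a grade new or worse than that patient's pre-RT grade, at a threshold fixed in advance, and compare arms on that.
- Replace the Chi-square test with a comparison adjusted for the pre-RT grade, such as logistic regression for a threshold or ordinal regression for the grade.

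Show raw prevalence by arm and visit as a supporting table, so that results can be set beside trials that report it. The choice should be fixed before outcome data by arm are examined.

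The cost is a few sentences of analysis wording. No new data, visits or patients are needed. Under the first form, reported toxicity rates will be lower than raw prevalence, and the report should say why.

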In addition, regional node area was not regularly irradiated in previous trials. 7%∼21% patients of the START trials received regional node irradiation (RNI). A follow-up was done after ten years, and no more arm and shoulder symptoms were observed in the HFRT group. However, these studies did not include internal mammary node (IMN) in the planning target volume. Therefore, the feasibility of hypofractionated RNI (including IMN irradiation) needs to be further investigated [18]. Based on the concerns mentioned above, it is necessary to reevaluate the effectiveness and safety of HFRT with SIB in BCS patients in the context of modern treatment strategies. A phase II trial of hypofractionated WBI (HF-WBI) combined with SIB in early breast cancer patients was conducted at our center, the results of which showed that HF-WBI and SIB could yield satisfactory cosmetic outcomes with mild toxicity. No patient developed severe radiodermatitis and the incidence of excellent/good breast cosmesis was 81.8% [19]. On the foundation of the results from our phase II trial and previous studies, a phase III multi-centered, randomized controlled trial was initiated to investigate the local control following normofractionated WBI with sequential boost (CFRTseq) versus moderately hypofractionated WBI with SIB (HFRTsib) with or without RNI in breast cancer patients after BCS.

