### Radiotherapy

#### Target volumes definition

Post-lumpectomy clinical target volumes (CTVs) include whole breast and post-operative tumor bed. When indicated, regional lymph nodes are also included. Target volume definitions are indicated below (Table 1) [20]. Gross target volume (GTV) of tumor bed should be contoured according to metal markers (usually titanium clips) placed during surgery and/or postoperative changes such as seroma. For patients without metal markers, postoperative changes should be clearly identified through simulation computed tomography (CT) and ultrasound. CTV of tumor bed is expanded from tumor bed GTV by 1 cm and is limited to the whole breast CTV. The planning target volumes (PTV) of whole breast and tumor bed should be expanded from CTV by 0.5 cm in all directions and be limited to 0.5 cm beneath the skin surface. The regional nodal area will be irradiated in patients with pathologically positive axillary lymph nodes either detected in sentinel lymph node biopsy or in axillary lymph node dissection. CTVs of the regional lymph nodal area include the undissected axilla (principally axillary level II and III), the supraclavicular nodes, and the internal mammary nodes. PTVs are expanded by 0.5 cm around the regional lymph node CTV.

**Table 1 Tab1:** Guidelines of CTV delineation

CTV	Cranial	Caudal	Medial	Lateral	Ventral	Dorsal
Breast	Upper border of palpable/visible breast tissue; up to the inferior edge of the sternoclavicular joint	Most caudal CT slice with visible breast/mammary fold	Medial border of palpable/visible breast tissue; maximally to the parasternal line	Lateral border of visible/palpable mammary gland	0.5 cm beneath skin surface (including visible breast tissue)	Anterior edge of the pectoralis major/intercostal muscles/ribs
Axillary level I	0.5 cm cranial to axillary vein	Level of 4th anterior rib, including postoperative change of SLNB	Axillary level II; chestwall	The line between pectoralis major and deltoid/ latissimus dorsi	Pectoralis major; pectoralis minor	Thoracodorsal vessels; the line between intercostal muscles and deltoid/ latissimus dorsi
Axillary level II	Cranial edge of axillary artery	Caudal edge of pectoralis minor	Medial border of pectoralis minor	Lateral border of pectoralis minor	Posterior surface of pectoralis minor	0.5 cm dorsal to axillary vein; anterior edge of the intercostal muscles

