
Another randomized trial concerning SIB in the context of HFRT is RTOG 1005, which compares SIB of 48 Gy/15 fractions with conventional sequential boost in breast-conserving patients [30]. The result of the study is pending. The trial HYPOSIB also discuessed SIB of 48 Gy/15fx in patients after BCS. The preliminary results were presented during the 2020 American Society of Clinical Oncology annual meeting, and initially proved the safety of HFRT with SIB technique [31]. In our center, a phase II trial investigating SIB technique irradiated the whole breast with 45 Gy in 25 fractions, and the dose to the tumor bed was simultaneously escalated to 60 Gy. The 5-year locoregional control rate for patients with invasive breast cancer was 98.7%, and none of the patients had grade 3 skin toxicity [32]. Our phase II trial with respect to HF-WBI combined with SIB in early breast cancer patients employed a total dose of 48 Gy to the tumor bed and 40 Gy to the whole breast, delivered in 15 fractions over the span of three weeks. The results showed well tolerance and favorable cosmetic outcomes, with no grade 3 radiodermatitis observed and an 81.8% satisfaction rate among patients regarding breast cosmesis. Two-year DFS rate was 98.6% [19]. Based on previous results, we will employ SIB in the HFRT arm compared with CFRTseq, the fractionation scheme used was the same as our phase II trial.

In the current trial, patients with positive axillary lymph nodes will receive RNI, and all the CTVs of RNI include IMN. According to EORTC 22,922 and MA. 20, RNI could significantly improve locoregional control in breast cancer patients with positive axillary nodes [33, 34]. Recent studies suggested that patients with medial/central tumors are likely to benefit from IMN irradiation (IMNI) [35, 36]. However, due to potential cardiac toxicity, the administration of IMNI remains controversial. The IMN region was not irradiated in previous trials regarding HFRT after BCS. In the current trial, IMNI will be delivered in all the patients receiving RNI. Dose to the heart should be strictly constrained and techniques such as deep inspiration breath hold (DIBH) will be applied to minimize heart dose. Major cardiovascular events will be documented during follow-up and early cardiac damage will be monitored through electrocardiography and echocardiography. Long-term results of our trial are expected to provide important data for the safety of hypofractionated IMNI.

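### The only stated toxicity comparison is between whole arms, although only node-positive patients receive nodal and internal mammary irradiation; toxicity should also be estimated within that randomisation stratum

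*Protocol article*

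**What the plan says.** Under Secondary endpoints, the protocol article says that "incidences of acute and late adverse events, cosmetic outcomes and quality of life (QoL) will be compared between the two groups". The Statistical analysis section supplies the method: "Comparison of toxicities and cosmetic results between the two groups will be performed with the Chi-square test". Both sentences take the randomised arm as the unit of comparison, and neither mentions RNI or nodal status.

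The arms are mixed in what they receive. Under Target volumes definition, "The regional nodal area will be irradiated in patients with pathologically positive axillary lymph nodes", and the Discussion adds that "In the current trial, IMNI will be delivered in all the patients receiving RNI". Node-negative patients in either arm have whole breast irradiation (WBI) without nodal fields.

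Nodal treatment is part of the stated reason for the trial. The Background says that "the feasibility of hypofractionated RNI (including IMN irradiation) needs to be further investigated". The Discussion describes recording of cardiovascular events with electrocardiographic and echocardiographic monitoring, and concludes: "Long-term results of our trial are expected to provide important data for the safety of hypofractionated IMNI".

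The Randomization section includes among its stratification factors "axillary lymph node status (positive vs. negative"), so the two arms are balanced by design among the patients who receive RNI.

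**The concern.** The stated comparison and the stated expectation concern different populations. Evidence on the safety of hypofractionated IMNI can come only from patients who receive it. In a whole-arm table, node-negative patients add to every denominator but cannot show a difference caused by nodal fields.

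Two consequences follow. The absolute excess is reported smaller than the excess RNI patients actually experience. And where the same toxicity also occurs after WBI alone, the background events add noise and the test loses power. The second case is realistic for some organs: Table 2 sets lung and heart constraints for WBI alone as well as for WBI + RNI, so node-negative patients have some exposure too.

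At stake is whether a reader of the final report could take a small or non-significant overall difference as reassurance about hypofractionated RNI with IMNI.

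**Working it through.** **The plan's own figure.** The article gives no rate, power or sample size for toxicity; its calculation concerns locoregional recurrence (LRR). It starts from the statement that "the five-year LRR of the CFRT group in the current trial is assumed to be 3" per cent, against 5% (HR 1.68), with one-sided alpha 0.025, 80% power, four years of recruitment and five years of follow-up. The number of events by Schoenfeld's formula is 4 × (1.96 + 0.842)² / (ln 1.68)² = 117. With exponential hazard −ln(0.97)/5, uniform accrual over four years and five further years, the event probability at the control rate is 0.0417, and 117 / 0.0417 gives about 2804. With the unrounded ratio ln(0.95)/ln(0.97) = 1.684 and unrounded events it is about 2770, against the stated 2766. Then 2766 × 1.05 = 2904. The size reproduces, but it says nothing about toxicity.

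**Inputs for the toxicity check**
- From the article: 1452 per group and 5% withdrawal, so 1452 × 0.95 = 1379 per group.
- Assumed, not in the documents: node-positive share f = 25% (range 15% to 35%); toxicity 10% versus 18% in RNI patients; a background rate b, equal in both arms, without RNI.

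**Dilution.** The whole-arm rate is f × (RNI rate) + (1 − f) × b. The background cancels in the difference, which is f × (18% − 10%): 1.2 points at f = 15%, 2.0 at 25% and 2.8 at 35%. This shrinkage does not depend on b.

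**Power.** Normal approximation, two-sided 0.05: power = Φ[(d − 1.96 × se0) / se1], where se0 = √(2p̄(1 − p̄)/n) and se1 = √((p1(1 − p1) + p2(1 − p2))/n).
- Whole arms, f = 25%, b = 5%: 6.25% versus 8.25%, n = 1379. (0.0200 − 1.96 × 0.00988) / 0.00987 = 0.065, power 53%.
- Whole arms, f = 25%, b = 0: 2.5% versus 4.5%, n = 1379. (0.0200 − 1.96 × 0.00700) / 0.00699 = 0.90, power 82%.
- RNI stratum, n = 1379 × 0.25 = 345 per group: (0.0800 − 1.96 × 0.0264) / 0.0263 = 1.07, power 86%.

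| Node-positive share | RNI stratum | Whole arms, b = 5% | Whole arms, b = 0 |
|---|---|---|---|
| 15% | 65% | 25% | 59% |
| 25% | 86% | 53% | 82% |
| 35% | 95% | 77% | 93% |

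At f = 25%, intermediate backgrounds of 2% and 1% give whole-arm power of 67% and 74%. The background rate therefore drives the power loss.

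**Other assumed rates.** With 1452 per group, f = 30% and 5% versus 10% in RNI patients, stratum power is 80%. Whole-arm power is 41% with a 5% background and 78% with none. The pattern is the same.

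**Would a stratified overall test be enough?** At f = 25% and b = 5%, a Cochran-Mantel-Haenszel (CMH) test stratified by axillary status has about 54% power, against 53% unstratified. It still averages over patients in whom no effect is possible.

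**The case against.** The strongest reply is that this is a condensed article with a very short analysis section. It names a test and two groups. It does not say that there will be a single test on all patients combined, and it does not rule out analysis by nodal status; stratum-specific safety tables commonly sit in the full protocol or SAP. A reader might infer that the trial has committed to one pooled toxicity test and will therefore miss RNI toxicity. The text does not support that: stratification by axillary status, separate dose constraints for WBI and WBI + RNI, and the cardiac monitoring all keep the stratum analysis available.

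A reader might also infer that the trial promises a formal answer on IMNI safety. It does not. The sentence is an expectation in the Discussion, IMNI safety is not a listed endpoint, and the Background frames the question as local control with or without RNI.

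Finally, every rate used above is assumed, and for toxicity that occurs only with nodal fields the whole-arm test loses little power.

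All of this stands as a limit on the point. What remains is that the article does state a comparison, that this comparison taken alone cannot support the stated expectation, and that the absolute excess is diluted whatever the background rate. Asking for the two statements to be aligned is not a complaint about missing detail.

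**Conclusion.** The point holds as a moderate improvement to a secondary endpoint. The dilution factor equals the node-positive share and follows from the design; its value is unknown because the documents do not give that share. Under the assumed 25%, an 8-point excess in RNI patients is shown as 2 points.

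The loss of power is conditional. It is large (53% against 86%) for a toxicity that also occurs at 5% without RNI, and slight (82% against 86%) for one that occurs only with RNI. A general claim that the whole-arm test would miss RNI-specific toxicity is therefore not supported; for such toxicity the main harm is an understated absolute risk. These figures rest on the assumed rates of 10% versus 18% and on 1379 evaluable patients per group. Nothing here touches the LRR analysis or the sample size.

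**What to change.** Add to the Statistical analysis section that arm/shoulder, lymphoedema, lung and cardiac toxicity will be estimated by arm, with confidence intervals for the difference, and compared between arms within the axillary-positive (WBI + RNI) randomisation stratum. Keep the overall comparison, add a treatment-by-stratum interaction check, and state that any conclusion on the safety of hypofractionated IMNI will rest on the axillary-positive stratum. A CMH test for the overall comparison is optional and does not by itself cure the dilution.

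The cost is analysis programming; no new patients or data are needed. The intervals will be wider: at f = 25% and 10% versus 18%, the 95% half-width within the stratum is 1.96 × √((0.10 × 0.90 + 0.18 × 0.82)/345) = 5.1 points. For the whole arms at 6.25% versus 8.25% it is 1.96 × √((0.0625 × 0.9375 + 0.0825 × 0.9175)/1379) = 1.9 points. There will also be more secondary comparisons, which should be labelled as supportive. Stating the analysis before late-toxicity results are known avoids its being read as a post-hoc subgroup.
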